### Study setting and subjects

Patients diagnosed with hypercholesterolaemia will be recruited from 9 family doctors' surgeries at 3 healthcare centres in the health care area of Albacete, Spain.

The inclusion criteria are: a) subjects diagnosed with limit hypercholesterolaemia (total cholesterol 200-249 mg/dl) or defined hypercholesterolaemia (total cholesterol equal to or above 250 mg/dl) who have LDL-cholesterol levels equal to or above 130 mg/dl, b) subjects aged 18 years or over attending the participating health centres, c) subjects who give their consent to participate after being informed of the study objectives. The exclusion criteria are: a) known hypersensitivity to sterol esters or to the other components of the food that contains them (liquid yoghurt), b) contraindication for treatment with sterol esters or any of the components of the food, c) physical disability that hinders collaboration, d) significant chronic organic or psychiatric disease, e) not obtaining informed consent.

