### Follow-up

The subjects will be followed-up for two years.

- Selection: patients who meet the inclusion criteria will be asked to participate in the study. After giving their informed consent they will be given an appointment for the initial visit and for the analytical tests.

- Initial visit: the participant will be randomised to one of the two groups. Their medical history will be taken and they will be given a physical examination. The corresponding dairy product will be dispensed (the following doses will be dispensed according to their expiry date). At this visit a lipid-lowering diet will be recommended to all the participants.

- Follow-up visits: at 1, 3, 6, 12, 18, and 24 months, the physical examination and analytical test parameters will be recorded. The cardiovascular risk will be calculated and possible adverse effects and compliance or adherence to the food supplied will be recorded.

The study will be finalised for the patient in the following circumstances: completed follow-up period (2 years), death, violation of the protocol, adverse event, intercurrent disease that makes it impossible to ingest food and patient abandons study or withdraws consent.

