### Primary variables and measuring methods

#### Primary variable

-Change in lipid profile at 1, 3, 6, 12, 18 and 24 months. Lipid levels will be measured in both plasma and capillary blood at the initial visit. The validity of the capillary blood lipid levels can be checked with the Cardiochek analyser (by total cholesterol, HDL-cholesterol and triglyceride strips, and subsequent calculation of LDL-cholesterol using the Friedewald formula). The measurements at 3, 12 and 24 months will be in plasma. At 1, 6 and 18 months they will only be in capillary blood.

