#### Efficacy analysis

After the prior stages of data purification, exploratory analysis and categorisation or transformation of variables, the following were performed:

-Comparison of the variables of interest and the stratification and potentially confounding variables in both groups at the start of the study. Although we used a random assignment system, we checked that the baseline values of the study variables were uniform over the two groups.

-Classification of the subjects of the two groups into different LDL-cholesterol and total cholesterol reduction levels. A baseline raw analysis will be performed to evaluate the following parameters and their 95% confidence intervals: ABI (absolute benefit increase), RBI (relative benefit increase) and NNT (number needed to treat). A stratified analysis will be performed adjusted for each independent variable.

-The incidence of the endpoint variables in the two groups will be described and compared at each follow-up period (comparison of means using Student's t tests or Mann-Witney U test, depending on the distribution of the variables). The Friedman test will be used to compare the changes in lipid profile throughout the study in each of the groups.

-The effect of the dairy product on total cholesterol and LDL-cholesterol levels will be determined, adjusted for changes in adherence to the prescribed regimen (linear models generalised for repeated means).

-The convergent validity of the capillary blood measurements compared to the plasma measurements will be analysed through intraclass correlation.

The analysis will be an intention to treat analysis including all randomised patients in the efficacy analysis, according to their group and regardless of the treatment received. A per-protocol analysis will also be performed for the primary variables. Intermediate analyses will be performed to decide if the study should be prematurely terminated in the event of frequent adverse effects or a clear improvement in the test group (see Figure 1 for the study flow chart).

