## Discussion

The results of this study will provide valuable information on the efficacy of plant sterol ester supplements in preventing cardiovascular disease by lowering plasma cholesterol levels and consequently cardiovascular risk. If this supplement were effective a sounder recommendation for the consumption of plant sterols in subjects with hypercholesterolaemia could be made.

Possible limitations of the study - using a randomisation procedure reduces the risk of selection bias as the investigator will not assign treatment and any factor that effects participation will be balanced in the two groups. Confounding will also be reduced as randomisation tends to divide the determinant factors, which influence the final result, equally between the two groups. However, bias could exist on collecting information due to the regression towards the mean effect or tendency of the continuous variables towards the mean in successive measurements, applicable to the analytical results. There is also a possible risk of differential loss to follow up between the two groups, due to the length of the study and also to the placebo effect which could contribute to the patients abandoning the study because they consider that the treatment provided is not having any effect.

The study protocol has been evaluated and approved by the Institutional Review Board of the Albacete Health Area on 23rd April, 2009. During the performance of the study the following ethical principles will be respected: voluntary participation with consent of the patient, guarantee of anonymity in the information provided by the patient, data provided by the patient exclusively restricted to use in the proposed study. The investigators will ensure that the study is conducted in accordance with the declaration of Helsinki and with legislation in effect (Royal Decree 223/2004) and the New Code of Medical Ethics of the Spanish Medical Association. The study will fully comply with Good Clinical Practice principles.

Finally, for the development of this project the following principles have been considered: 1) data on the dairy product are sufficient to guarantee that the risk to the study participants is acceptable; 2) the objectives of the study will probably provide further knowledge of the topic to be studied; 3) the available information warrants the performance of this study and its potential risk to the participants.

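### The within-arm Friedman test of the lipid time course mixes plasma and capillary visits and never compares the arms, so it cannot support a conclusion about the product

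*Protocol article*

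**What the plan says.** The Efficacy analysis section lists several analyses. The one at issue is a time-course test run separately in each arm: "The Friedman test will be used to compare the changes in lipid profile throughout the study in each of the groups".

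The Primary variable section sets the measurement method by visit. At baseline, "Lipid levels will be measured in both plasma and capillary blood at the initial visit". After that, "The measurements at 3, 12 and 24 months will be in plasma", and "At 1, 6 and 18 months they will only be in capillary blood". Capillary LDL is calculated by the Friedewald formula from strip readings. For the relation between the two methods, the Efficacy analysis section plans only this: "The convergent validity of the capillary blood measurements compared to the plasma measurements will be analysed through intraclass correlation".

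Three further statements bear on change within an arm:
- Entry is limited to people "who have LDL-cholesterol levels equal to or above 130 mg/dl" (Study setting and subjects).
- At the initial visit, when participants are randomised, "At this visit a lipid-lowering diet will be recommended to all the participants" (Follow-up).
- The Discussion concedes that "bias could exist on collecting information due to the regression towards the mean effect".

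The Efficacy analysis section also plans between-arm t or Mann-Whitney tests at each follow-up visit, and a repeated-measures linear model for the effect of the product. It promises an intention-to-treat analysis of everyone randomised.

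**The concern.** A Friedman test asks whether the visits differ within one group of people. Here four things can make them differ without any action of the product:

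1. **Method.** Visits alternate between capillary strips and plasma. Any systematic offset between the two appears as a visit effect, and visit and method cannot be separated.
2. **Diet.** Both arms receive dietary advice at the start, so a fall in both is plausible.
3. **Regression to the mean.** Participants are selected on a high LDL value.
4. **Other treatment.** The Intervention section lets participants continue existing lipid-lowering treatment and start new treatment.

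The test is listed among the efficacy analyses and is not labelled descriptive. The risk is that a significant active-arm result, or significance in the active arm only, is reported as evidence for the product. Comparing two within-arm p-values is not a test of the difference between arms.

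The standard Friedman test also needs complete blocks: a participant who misses one visit drops out altogether. With 20% loss to follow-up assumed over 24 months, that sits badly with an analysis of all randomised patients.

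**Working it through.** **The plan's own figure.** Inputs from the Sample size section: mean LDL 157 mg/dl, SD 30, 10% reduction (15.7 mg/dl), two-sided alpha 0.05, power 90%.

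n per arm = 2 × (1.960 + 1.282)² × 30² / 15.7² = 76.7, or 77 rounded up. The article states 76 per arm; power at 76 is 89.7%. The figure is reproduced within rounding, and 76 per arm is used below.

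**Assumptions not in the documents.** Between-subject SD 26 and within-subject SD 15 (√(676 + 225) = 30.0, matching the stated SD); capillary offset 3, 5 or 8 mg/dl; diet effect 5 mg/dl; regression to the mean from truncating at 130 a population with mean 145.

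**Why a small offset matters.** There are seven time points: plasma baseline, then months 1, 3, 6, 12, 18 and 24, so three capillary and four plasma. With an offset d and nothing else, a capillary value exceeds a plasma value in the same person with probability p = Φ(d / (15√2)). The expected mean rank moves from 4 by +4(p − 0.5) at capillary visits and by −3(p − 0.5) at plasma visits. The noncentrality is 12n / (k(k + 1)) × Σ(shift²), with n = 76 and k = 7, so the multiplier is 912/56 = 16.29. The critical value on 6 df is 12.59.

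For d = 5: p = Φ(0.2357) = 0.593; shifts +0.373 and −0.280; Σ = 3 × 0.373² + 4 × 0.280² = 0.73; noncentrality 11.9; rejection probability about 73%.

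| Offset (mg/dl) | Approximation | Simulation, 2,000 runs |
|---|---|---|
| 3 | 29% | 28% |
| 5 | 73% | 74% |
| 8 | 99% | 99% |

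**All artefacts, no product effect (simulated).**

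| Scenario | Friedman, control | Friedman, active | Active significant only | Between-arm t, 24-month change |
|---|---|---|---|---|
| None | 4.7% | 5.2% | 4.8% | 5.3% |
| Offset 3 | 27.8% | 28.0% | 20.8% | 5.4% |
| Offset 5 | 74.0% | 74.0% | 18.9% | 5.0% |
| Offset 8 | 99.4% | 99.3% | 0.6% | 4.7% |
| Diet 5 | 39.8% | 38.8% | 23.9% | 5.2% |
| Regression to the mean | 24.4% | 24.4% | 18.8% | 5.2% |
| All three, offset +5 | 94.6% | 95.3% | 5.3% | 5.0% |
| All three, offset −5 | 100% | 100% | 0.1% | 5.4% |

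**Sensitivity.** With within-subject SD 10 or 20 (1,000 runs each), an offset of 5 gives about 98% or 42%, and all three artefacts together give 89% to 100%. The between-arm test stays at 4.3% to 6.1%.

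**With a true effect.** Given a 15.7 mg/dl product effect and all three artefacts (500 runs), Friedman rejects in 95% of control arms and 100% of active arms, so it hardly separates them. The between-arm test has 99.8% power in this model.

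**What the intraclass correlation shows.** Assume between-subject variance 900 and error variance 100. The ICC is 900/1000 = 0.90. For absolute agreement between two methods, an offset of 5 adds 5²/2 = 12.5 to the denominator: 900/1012.5 = 0.89. A consistency ICC would not move at all. A high ICC is therefore compatible with an offset that makes the Friedman test reject in about three arms in four.

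**The case against.** A reader might infer that the plan will treat device, diet and regression to the mean as product effect. The article does not say so. It words the Friedman test as a comparison inside each group, and gives the product effect to the between-arm tests at each visit and to the repeated-measures model. Both arms share the visit schedule, measurement method, diet advice and entry threshold, so these artefacts cancel on average between arms; the simulated between-arm test held its level. The Discussion also acknowledges regression to the mean. All of this stands, and it limits the point to the time-course analysis.

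The size is assumed: no figure in the article shows that a capillary offset exists. A diet-induced fall is moreover a real within-arm change, so rejecting because of it is not a false positive for change over time. Both points stand; the second only confirms that the test answers a question other than the trial's.

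The article does not say outright that both methods enter one test, and separate series are possible because baseline is taken both ways. But the test is described as covering the whole study, with no split by method, and followed as written it mixes them.

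Missing-data handling may be set out elsewhere, and imputation would avoid losing incomplete participants. A contradiction with the intention-to-treat statement is therefore not proved; only the standard form of the test conflicts with it.

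**Conclusion.** The point holds for the time-course analysis. The Friedman test as specified cannot support a conclusion about the product: it makes no between-arm comparison, its visits alternate between methods, and it responds to changes expected in both arms. Under assumed offsets of 3 to 8 mg/dl it rejects in roughly 28% to 99% of arms with no true change, and significance in the active arm alone arises in up to about 24% of null trials under a moderate artefact, against 4.8% with none. These percentages rest on the assumed offsets, diet effect and variance split; the structural fault does not.

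The finding does not reach the planned between-arm tests or the repeated-measures model, which these shared artefacts do not bias. It is a fault worth correcting in a stated analysis, not a threat to the main comparison.

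**What to change.** - Base time-course inference on arm-by-visit contrasts from the repeated-measures model already planned, using all available visits.
- Compute change against the same-method baseline: plasma for months 3, 12 and 24; capillary for months 1, 6 and 18.
- Drop the Friedman test, or keep it as descriptive only and within a single measurement method. State that a result significant in one arm only is not evidence of efficacy.
- Report the mean capillary-plasma difference with limits of agreement beside the intraclass correlation.

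The cost is a change of wording and a little more analysis work. Both baselines are already collected, so no measurements are added. The downside is that each single-method trend has fewer time points: baseline and three follow-up visits.

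### The only between-arm repeated-measures model adjusts the product effect for post-randomisation changes in adherence, so its arm coefficient does not in general estimate the effect of assignment

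*Protocol article*

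**What the plan says.** The Efficacy analysis section of the protocol article lists several analyses.

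- **Repeated-measures model.** "The effect of the dairy product on total cholesterol and LDL-cholesterol levels will be determined", and the same sentence continues "adjusted for changes in adherence to the prescribed regimen (linear models generalised for repeated means".
- **Visit-by-visit comparison of arms.** Outcomes are described and "compared at each follow-up period (comparison of means using Student's t tests or Mann-Witney U test, depending on the distribution of the variables".
- **Within-arm change over time.** "The Friedman test will be used to compare the changes in lipid profile throughout the study in each of the groups".
- **Classified responses.** Patients are grouped by level of LDL- and total-cholesterol reduction and summarised by absolute and relative benefit increase and number needed to treat, with a stratified analysis to follow.

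The section then sets the principle: "The analysis will be an intention to treat analysis including all randomised patients in the efficacy analysis", by assigned group and whatever treatment was received. A per-protocol analysis is listed separately. No analysis is named as primary, and the adherence-adjusted model is not called supplementary or exploratory.

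On timing, the Follow-up section places randomisation at the initial visit. The lipid-lowering diet is recommended at that same visit. At the later visits, "possible adverse effects and compliance or adherence to the food supplied will be recorded".

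**The concern.** The repeated-measures model is the only listed analysis that both compares the arms and uses all visits together. It is also the one described as determining the product's effect on cholesterol. Its covariate, change in adherence, arises after assignment.

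Conditioning on a variable that assignment may influence has two possible consequences. If adherence carries part of the product's effect, holding it fixed removes that part. If adherence shares unmeasured causes with LDL-cholesterol, such as general health behaviour or use of lipid-lowering drugs, holding it fixed makes the arms differ in those causes even though randomisation had balanced them. Either way the arm coefficient departs from the effect of assignment, and a larger sample does not remove the departure.

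At stake is the interpretation of the one overall longitudinal estimate. It could understate or overstate a real effect, or show a difference when there is none, and the text gives the reader no warning that it answers a different question from the intention-to-treat comparison.

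**Working it through.** **1. Is the covariate post-randomisation on either reading?** The word regimen could mean the yoghurt or the diet. Yoghurt adherence is recorded at the follow-up visits. Dietary adherence can only concern advice given at the randomisation visit. Changes in either arise after assignment, so this is not baseline adjustment.

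**2. Is any other listed analysis both between-arm and longitudinal?** The t or Mann-Whitney tests compare arms one visit at a time. The Friedman test looks across visits within one arm. The benefit-increase and number-needed-to-treat measures use classified reductions. None is both.

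**3. The plan's own effect size.** From the Sample size section: mean LDL-cholesterol 157 mg/dl, SD 30, 10% reduction, 90% power, two-sided alpha 0.05.

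- Difference: 0.10 × 157 = 15.7 mg/dl.
- n per arm = 2 × (1.960 + 1.282)² × 30² / 15.7² ≈ 76.7, or 77 rounded up, against the stated 76. Power at 76 per arm is 0.897.

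The planned figure reproduces within rounding. It is used here only for scale: effect -15.7 mg/dl, total SD 30.

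**4. Bias when adherence enters the model.** The documents give no adherence data, so the inputs below are assumptions. Let Z be the arm (1 = active), U an unmeasured prognostic factor with SD 1, and A adherence:

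- A = a·Z + U + e, with e of SD 1
- LDL = θ·Z + b·U + noise, total SD about 30

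Within an arm, the slope of LDL on A is b × Var(U)/Var(A) = b × 1/(1 + 1) = b/2. The arm coefficient adjusted for A is therefore θ - a·b/2, so the bias is -a·b/2. The coefficient without A is θ.

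Formula and simulation (400,000 patients per scenario, least squares at one time point), in mg/dl:

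| a | b | bias -a·b/2 | adjusted, θ = -15.7 | adjusted, θ = 0 |
|---|---|---|---|---|
| -0.3 | -15 | -2.25 | -18.02 | -2.20 |
| -0.3 | -8 | -1.20 | -16.84 | -1.06 |
| 0 | -15 | 0 | -15.52 | -0.11 |
| 0.3 | 0 | 0 | -15.68 | 0.00 |
| 0.3 | -8 | +1.20 | -14.49 | +1.11 |
| 0.3 | -15 | +2.25 | -13.53 | +2.22 |
| 0.5 | -8 | +2.00 | -13.65 | +2.03 |
| 0.5 | -15 | +3.75 | -11.97 | +3.78 |

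Across all scenarios the coefficient without A stayed between -15.9 and -15.5 (truth -15.7) or between -0.2 and +0.2 (truth 0), which is simulation error.

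**5. Reading the result.** By the formula, a true 15.7 mg/dl reduction is overstated by up to 2.25/15.7 = 14% or understated by up to 3.75/15.7 = 24%. The sign follows the direction in which assignment shifts adherence. The bias is zero when a = 0, and in this set-up also when b = 0. The set-up contains only the shared-cause path. If adherence also carried part of the product's effect, that would be a further departure not counted here.

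**The case against.** The strongest reply has four parts.

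**A randomised contrast exists elsewhere.** The unadjusted comparisons at each visit match the specific objectives, which are set visit by visit, and the sample size is itself a two-mean calculation. This stands. A reader might infer that the trial has no valid randomised estimate, or that its answer rests on the adherence-adjusted model. The documents support neither, because they do not rank that model above the others.

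**The model need not contradict the intention-to-treat statement.** That statement is put in terms of population and group: "including all randomised patients in the efficacy analysis, according to their group and regardless of the treatment received". A covariate-adjusted model can include every patient in the assigned arm and meet those words. This also stands. A reader might infer a flat contradiction, but the problem is what the coefficient estimates, not who is analysed.

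**Timing alone does not create bias.** If regimen means the diet, the products look identical and everyone is blinded, there is little documented reason for dietary adherence to differ by arm, and the bias would be about zero. This stands as a possibility, but the text neither settles the reading nor secures the condition. The documented support for an arm effect on adherence is modest: occasional mild digestive effects of phytosterols, and a Discussion remark about "the placebo effect which could contribute to the patients abandoning the study because they consider that the treatment provided is not having any effect". That remark concerns leaving the study, not adherence among those analysed. The documents do not say that patients are told their lipid results, so that route is not relied on.

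**The size is illustrative.** It comes from a single-time model on adherence level with assumed inputs, while the plan has repeated measures and change in adherence. This is accepted. The figures show plausible scale and both directions, and are not a prediction.

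**Conclusion.** The point holds for this one model. As written, the only between-arm repeated-measures analysis gives an arm coefficient at equal adherence change, and that does not in general equal the effect of assignment. It is biased if assignment affects adherence and adherence either mediates the effect or shares causes with LDL-cholesterol. It is about unbiased if assignment does not affect adherence.

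Under the assumed range (arm shift -0.3 to +0.5 units, shared-cause effect 0 to -15 mg/dl per SD), a true -15.7 mg/dl is estimated at about -18.0 to -12.0, and a true zero at about -2.2 to +3.8. It would go too far to call the bias certain or always towards the null: the range runs both ways and includes none.

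Because unadjusted comparisons at every visit are also planned, this should be fixed but does not undermine the trial's efficacy analysis as a whole.

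**What to change.** In the Efficacy analysis section, fit the repeated-measures model on all randomised patients by assigned arm without the adherence term. Adjust only for baseline values already collected, such as baseline LDL-cholesterol. If an adherence-adjusted model is still wanted, keep it under a label saying that it is supplementary and does not estimate the randomised effect, and state whether adherence means the yoghurt or the diet.

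The change is to wording only. It needs no new data or visits and leaves the planned sample size of 152 evaluable patients as it is.

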### Sample size

To obtain a 90% statistical power with an alpha error of 0.05 (bilateral hypothesis). The effect to be demonstrated is based on the following:

- The expected mean value of LDL-cholesterol in the patients included in the study is 157 mg/dl ± 30 SD (value obtained in previous studies conducted in a Spanish population).

- To demonstrate an effect of a 10% reduction in LDL-cholesterol in patients who receive the supplements, 152 subjects are needed (76 in the active group and 76 in the placebo group).

Assuming a 20% loss to follow up, 182 subjects will need to be selected and will be distributed equally between the two groups in order to obtain the maximum statistical power.

The recruitment period will be from January 2010 to September 2010.

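### Capillary–plasma agreement is summarised only by an intraclass correlation, which does not show the mean shift between methods, although three of the six primary visits are capillary-only

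*Protocol article*

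**What the plan says.** The primary variable is "Change in lipid profile at 1, 3, 6, 12, 18 and 24 months" (Primary variable section). The method alternates over those visits: "The measurements at 3, 12 and 24 months will be in plasma", and "At 1, 6 and 18 months they will only be in capillary blood". Both methods are used together once: "Lipid levels will be measured in both plasma and capillary blood at the initial visit". Capillary LDL is not read directly. It comes from three strip readings and "subsequent calculation of LDL-cholesterol using the Friedewald formula".

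The Efficacy analysis section gives one analysis of agreement: "The convergent validity of the capillary blood measurements compared to the plasma measurements will be analysed through intraclass correlation". It does not state the form of the coefficient. The same section compares the groups at each follow-up, applies a Friedman test within each group over the course of the study, and sorts patients into levels of LDL and total-cholesterol reduction to obtain the absolute benefit increase (ABI), the relative benefit increase (RBI) and the number needed to treat (NNT). Under Follow-up, cardiovascular risk is calculated at every follow-up visit.

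**The concern.** An ICC expresses disagreement relative to the spread between patients. In its consistency form it ignores a constant difference between methods. In its absolute-agreement form the difference lowers the coefficient, but it is merged with random error and divided by patient spread, so it cannot be read off in mg/dl. Here the outcome is change over visits that switch method, so the quantity needed is the mean capillary-minus-plasma shift.

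If that shift is sizeable and goes unreported, any analysis that sets capillary beside plasma values takes a change of method for a change in lipids. A Friedman test over the alternating series would show an artificial rise or fall at months 1, 6 and 18. A capillary value compared with a plasma baseline would move patients across a reduction cut-off. Risk scores at those three visits would carry the shift.

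**Working it through.** **Inputs from the protocol.** Sample size section: "The expected mean value of LDL-cholesterol in the patients included in the study is 157 mg/dl ± 30 SD", and a target reduction of 10%, so 0.10 × 157 = 15.7 mg/dl. Number to be selected: 182. Capillary-only visits: 3 of 6, or 50%.

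**Reproducing the plan's own figure.** At 90% power and two-sided 0.05, n per group = 2 × [30 × (1.960 + 1.282) / 15.7]² = 76.7. The plan has 76 per group, which gives 89.7% power. This agrees to within rounding and confirms 30 and 15.7 as the working inputs.

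**Assumptions.** The protocol gives neither the measurement error nor the shift. I take a random error SD e of 5, 8 or 10 mg/dl per method, and a constant capillary shift b of 10 mg/dl, or of 15.7 mg/dl as an extreme equal to the whole target effect.

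**ICC.** With S = 30:
- consistency form: S² / (S² + e²)
- absolute-agreement form: S² / (S² + e² + b²/2)

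| e (mg/dl) | Consistency, any b | Agreement, b = 10 | Agreement, b = 15.7 |
|---|---|---|---|
| 5 | 900/925 = 0.97 | 900/975 = 0.92 | 900/1048.2 = 0.86 |
| 8 | 900/964 = 0.93 | 900/1014 = 0.89 | 900/1087.2 = 0.83 |
| 10 | 900/1000 = 0.90 | 900/1050 = 0.86 | 900/1123.2 = 0.80 |

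This treats 30 as the SD of true values. If 30 already contains the measurement error, the numerator is S² − e² and the denominators are S² and S² + b²/2. The ranges become 0.89–0.97, 0.84–0.92 and 0.78–0.86, so the message is the same.

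**What the same pairs could show.** The SD of a paired difference is e√2. The 95% limits of agreement lie 1.96 × e√2 either side of the mean difference: ±13.9, ±22.2 or ±27.7 mg/dl. The 95% confidence interval for the mean shift from 182 pairs is 1.96 × e√2 / √182 = ±1.0, ±1.6 or ±2.1 mg/dl. The shift is therefore well estimable from data already planned.

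**Group comparison at one visit.** With a constant shift b in both arms, (placebo mean + b) − (active mean + b) = placebo mean − active mean. The bias is 0.

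**Friedman test within a group.** I simulated 76 patients, six visits and no true change, with the shift added at months 1, 6 and 18 and an assumed within-patient SD of 8 to 20 mg/dl. A shift of 10 mg/dl gave p < 0.05 in 97–100% of runs, a shift of 5 mg/dl in 41–100%, and no shift in about 4–7%.

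**Reduction categories.** This illustration takes a cut-off of 15.7 mg/dl, an assumed SD of change of 25, and mean reductions of 15.7 (active) and 0 (placebo). Capillary values are set against a plasma baseline.

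| Shift | Active reaching cut-off | Placebo reaching cut-off | RBI | NNT |
|---|---|---|---|---|
| 0 | 0.500 | 0.265 | 0.89 | 4.3 |
| +10 | 0.345 | 0.152 | 1.27 | 5.2 |
| −10 | 0.655 | 0.410 | 0.60 | 4.1 |

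A shift common to both arms does not cancel here.

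**The case against.** The strongest reply is that the trial's question is the difference between randomised, blinded groups, and at any visit both groups are measured the same way. A constant shift then has no effect on that comparison, and months 3, 12 and 24, including the last visit, are in plasma anyway. This stands, and it sets the limit of the point. It covers a constant shift only: an error proportional to the level would rescale the difference (10% would turn 15.7 into 17.3 mg/dl), and extra random error costs power.

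A second reply is that both methods are measured at the initial visit, so change can be taken like for like, and nothing in the article says a plasma baseline is subtracted from a capillary value or that the Friedman test pools the methods. This also stands. The exposure is conditional on mixing, which the text neither prescribes nor rules out.

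A third is that ICC form and acceptance bounds belong in a full analysis plan. That is fair, and their absence is not the point. The point is that the article names a statistic that does not report the quantity this design needs.

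Two stronger readings are tempting and should be resisted. A reader might infer that a good ICC licenses the mixing of methods. The article attaches no threshold or consequence to it, and the capillary visits are fixed whatever it shows. A reader might also argue that entry restricted to patients "who have LDL-cholesterol levels equal to or above 130 mg/dl" narrows the spread below 30 and so changes the ICC. The Sample size section gives 157 ± 30 for patients included in the study, so cutting that distribution at 130 again would apply the selection twice.

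**Conclusion.** The point holds in a limited form. ICC is the only agreement measure named, and it can read about 0.86 to 0.97 while capillary values are off by 10 mg/dl, which is 10/15.7 = 64% of the target effect. At a shift equal to the whole effect, a consistency ICC is unchanged, but an absolute-agreement ICC falls to about 0.8, which a careful reader might notice. The figures rest on the protocol's SD of 30 and on assumed errors of 5 to 10 mg/dl. Nothing in the document indicates that a shift of this size exists.

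A reader might conclude that the efficacy result is biased. The document does not support that, because a constant shift drops out of the group comparison at each visit. What is exposed is the within-group Friedman series if methods are mixed, the reduction categories with ABI, RBI and NNT if baseline and follow-up differ in method, and cardiovascular risk at months 1, 6 and 18. I rate this an optional improvement.

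**What to change.** In the Efficacy analysis section, replace the ICC as the sole measure. From the paired initial-visit values, report the mean capillary-minus-plasma difference with its 95% confidence interval and Bland–Altman limits of agreement, with a check for trend across the range. Keep an absolute-agreement ICC as a supplement. State that change at months 1, 6 and 18 is taken from the capillary baseline and change at months 3, 12 and 24 from the plasma baseline, including for the reduction categories. Do not run the Friedman test on raw values of mixed method. When reporting cardiovascular risk at months 1, 6 and 18, say that it rests on capillary lipids and compare it with a baseline risk from capillary lipids.

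The cost is a few lines of analysis. The pairs are already planned, and no further samples or visits are needed. One limit remains: pairs exist only before treatment, so later drift between the methods cannot be checked from them.
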